# Randomized phase II selection trial of FLASH and conventional radiotherapy for patients with localized cutaneous squamous cell carcinoma or basal cell carcinoma: A study protocol

**DOI:** 10.1016/j.ctro.2024.100743

**Published:** 2024-02-08

**Keywords:** FLASH radiotherapy, Ultra high dose rate, Skin cancer, Squamous cell carcinoma, Basal cell carcinoma

## Abstract

•Basal cell carcinoma (BCC) and squamous cell carcinoma (SCC) are the most prevalent skin cancers in western countries.•In pre-clinical studies FLASH-RT induces a remarkable sparing of normal tissues, while preserving intact anti-tumor efficacy.•LANCE is a randomized selection phase II trial of FLASH-RT versus CONV-RT for patients with T1-T2 N0 BCC or SCC of the skin.•This is the first randomized trial evaluating FLASH-RT and CONV-RT in a curative setting.

Basal cell carcinoma (BCC) and squamous cell carcinoma (SCC) are the most prevalent skin cancers in western countries.

In pre-clinical studies FLASH-RT induces a remarkable sparing of normal tissues, while preserving intact anti-tumor efficacy.

LANCE is a randomized selection phase II trial of FLASH-RT versus CONV-RT for patients with T1-T2 N0 BCC or SCC of the skin.

This is the first randomized trial evaluating FLASH-RT and CONV-RT in a curative setting.

## Introduction/rationale

Basal cell carcinoma (BCC) and squamous cell carcinoma (SCC) are the most prevalent skin cancer types in western countries, and represent more than 5 million cases annually in the United States with an increasing prevalence in Europe over the last decades [1]. Several therapeutic options are available such as surgical excision, conventional external radiation therapy (CONV-RT), cryotherapy, brachytherapy and topical treatments. While surgical excision is considered to be the primary curative treatment approach of cutaneous SCC and BCC, CONV-RT with conventional dose rate (0.03–0.06 Gy/sec) is recognized as an alternative treatment for well selected patients [2], [3], [4], [5]. In this frame, radiotherapy is generally delivered over a few weeks (2 to 8) which is not convenient for elderly patients who frequently present co-morbid conditions and have transfer issues. Moreover, CONV-RT routinely generates skin side effects for patients. According to CTCAE classification, a grade ≥ 2 radiation-induced acute toxicity such as dermatitis, mucositis and pain can be found in up to 20–70 % of patients after CONV-RT treatment and a late skin radio-necrosis in up to 6 % of patients after a single fraction treatment [6], [7], [8]. Other esthetical complications such as dyspigmentation and telangiectasia are also observed in 65–70 % of patients^9^.

The FLASH phenomenon, consisting in a remarkable sparing of healthy tissues with less side effects as compared to CONV-RT, was consistently described in preclinical setting [10]. For instance, one of the most striking result comes from the dose escalation experiment comparisons between CONV-RT and FLASH-RT on the skin of a mini-pig [11]. Single irradiation doses escalating from 22 Gy to 34 Gy were delivered to the same animal and at the same time. In comparison to 25 Gy delivered with low energy electron CONV-RT (dose rate ≈ 0.08 Gy/s), a dose of 34 Gy delivered with low energy electron FLASH-RT (dose rate ≈ 300 Gy/s) produced comparable results. Interestingly, severe late skin fibronecrosis was observed only with CONV-RT, assessing the sparing effect of FLASH-RT on the skin of the pig, especially from severe late effects. Comparable observations were collected across animal species (i.e., zebrafish, mice, mini-pig and cat), while providing an efficient anti-tumor effect [10]. The rational for clinical translation of FLASH-RT is based on the robustness and reproducibility of these results.

In this clinical trial, patients with localized T1-T2 N0 M0 cutaneous SCC and BCC who cannot undergo or decline surgical resection will be treated by a definitive curative radiotherapy and randomized between FLASH-RT or CONV-RT. Lesions will be divided into so called “small” and “large” volume groups. Small lesions are defined as T1 lesions (≤20 mm) whereas large lesions are defined as T2 lesions (>20 - ≤ 40 mm), according to the TNM UICC, 8th Edition. A single dose of 22 Gy will be delivered for lesions in “small volume” arm. A 22 Gy single dose FLASH therapy has already been tested in the ongoing CHUV-DO-0023-IMPulse-2020 dose escalation clinical trial (NCT04986696) and was shown to be safe when applied on skin metastases of melanoma of an overall volume ≤ 30 cc (data not yet published). The data from the ongoing IMPulse trial (NCT04986696) are re-assuring regarding the expected tolerance of the 22 Gy dose level in FLASH, and both SCC and BCC are less radioresistant than melanoma. For lesions in “large volume” arm, a dose of 30 Gy in 5 fractions (over 2 weeks) will be administered. It represents the minimal hypofractionated dose admitted for the treatment of skin lesions according to NCCN guidelines2, [4], [5], [16]. A grade ≥ 2 skin toxicity can be found in 20–70 % of patients (mainly radiation dermatitis, mucositis or pain) after CONV-RT in this range of dose [7], [17], [18].

In this context, our main hypothesis is that FLASH-RT will be well tolerated (primary endpoint) and efficient (hierarchically tested primary endpoint) in a population of patients with localized cutaneous SCC and BCC. LANCE trial represents the first curative intent FLASH trial.

## Design

This is an open-label single center randomized selection, non-comparative phase II study of FLASH-RT versus CONV- RT in patients with localized cutaneous SCC or BCC non-amenable to surgery, as per tumor board assessment.

Patients will be randomly allocated to the FLASH-RT arm or to CONV-RT (according to standard guidelines) [4], [6], [16] treatment arm, as described below **(**Fig. 1**,**
Fig. 2**)**:

**Fig. 1 f0005:**
[figure not shown]
Overview of the study design for small volume lesions.

**Fig. 2 f0010:**
[figure not shown]
Overview of the study design for large volume lesions.

*For T1 (small, ≤ 20 mm) lesions*
***:***
­Arm A: 22 Gy single dose FLASH-RT­Arm B: 22 Gy single dose CONV-RT

For FLASH-RT arm, a 9 MeV electron FLASH-RT will be delivered in 10 pulses of 2.2 Gy each, delivered at a pulse repetition frequency of 90 Hz for a total delivery time of 100 ms, corresponding to a mean dose rate of 220 Gy/s.

For CONV-RT arm, a 10 MeV electron CONV-RT will be delivered at a conventional dose rate (approximately 2–8 Gy/min) with a clinical linac. A bolus of 5–10 mm will be used to compensate for the difference in beam penetration between the FLASH-RT and CONV-RT arms.

*For T2 (large, >20 – ≤ 40 mm) lesions*
***:***
­Arm A: 5 x 6 Gy fractionated dose FLASH-RT (5 fractions in less than 2 weeks)­Arm B: 5 x 6 Gy fractionated dose CONV-RT (5 fractions in less than 2 weeks)

For FLASH-RT arm, a 9 MeV electron FLASH-RT will be delivered in 3 pulses of 2 Gy each, delivered at a pulse repetition frequency of 90 Hz for a total delivery time of 22 ms, corresponding to a mean dose rate of 270 Gy/s.

For CONV-RT arm, the same beam parameters as in the small CONV-RT arm will be used with a dose adaptation.

Inclusion and exclusion criteria are shown in Table 1.

**Table 1 t0005:** Inclusion and exclusion criteria.

Inclusion criteria	Exclusion criteria
Signed study Informed Consent Form Karnofsky Performance Status (KPS) ≥ 60 % Age ≥ 60 years Patients with histologically proven cSCC or BCC Patients requiring radiotherapy treatment according to dermato-oncology tumor board: patients who cannot undergo surgical procedure or patients who decline surgical resection and/or anatomical locations where surgery can compromise function or cosmesis.T1-T2 N0 M0 lesions with a small (T1; lesion ≤ 2 cm in diameter) or large (T2; 2 cm < lesion ≤ 4 cm) volume (TNM UICC, 8th Edition) Lesions should be at least 4 cm apart if treated with 2 different modalities (including surgical treatment of lesions). Lesions should not be located on the face, except on the forehead, above a line situated 1 cm above the eyebrows. Lesions located on the scalp can be treated	Previous radiotherapy in the treated area Concomitant auto-immune disease with skin lesions Concomitant use of radio-sensitizer drug Cognitive disorders, not compatible with the signature of informed consentCurrent, recent (within 10 days prior start of study treatment), or planned participation in an experimental drug study (before EOT visit)Concomitant use of systemic oncological treatment for a cancer other than the skin cancer (s)

## Objectives and endpoints

### Objective

The aims of the study are to describe and compare the toxicity and efficacy of FLASH-RT to CONV-RT (according to the dose per lesion size) through a randomized phase II selection study in patients presenting localized cutaneous SCC or BCC requiring a radiotherapy treatment.

### Endpoints

Primary endpoint•Safety measured by ≥ grade 3 skin toxicity up to 6 weeks after radiotherapy

Hierarchically tested primary endpoint.•Hierarchically tested efficacy measured by local control rate

Safety will be measured by ≥ grade 3 skin toxicity as defined by Common Terminology Criteria for Adverse Events (CTCAE v5.0) [8]. Local control rate is censured by any histologically proven local relapse into the initial treatment field up to one year post randomization.

Secondary endpoints•Acute side effects in the treatment field•Late side effects in the treatment field (≥3 months)•Blinded Imaging Central Review (BICR) of photographs evaluating both tumor response and “in radiation field” normal tissues reaction around the treated tumors•Optical coherence tomography (OCT) examination of the irradiated skin will be compared to the normal non-irradiated skin at baseline, 4 weeks, 6 months, and 12 months post-treatment

## Statistical design

This is a randomized phase II selection design with two treatment arms, where each individual arm is structured as an independent single-arm phase II study [19]. In this setting, randomization is primarily for the purpose of reducing various types of bias, such as patient selection bias and controlling for known or unknown baseline imbalances between arms.

Each arm will be evaluated separately, with hierarchical testing of 1. Safety and 2. Efficacy as measured by local tumor control rate.

### Safety evaluation (for each study arm separately)

The safety will be evaluated based on a Simon’s two-stage design with targeted rate of skin toxicity of grade ≥ 3 (π^s^; number of lesions with at least one skin toxicity of grade 3 or higher, up to 6 weeks after radiotherapy, among all treated lesions) less than 10 %, and considering as unacceptable, a rate of 25 %. That is, we test the null hypothesis H_0_: π^s^_0_ ≥ 25 % versus the alternative H_1_: π^s^_1_ < 25 %, evaluated at π^s^_1_ = 10 %.

A sample size of 48 lesions (of small or large size) per study is needed to test the above hypothesis, at a one-sided 5 % type I error and power of 80 %.

If at the interim evaluation (first stage of Simon’s two-stage design), more than 10 lesions in the first 13 evaluated lesions do not present with skin toxicity of grade ≥ 3, the study arm will continue to accrual completion. If more than 40 out of the 48 lesions, do not present with skin toxicity of grade ≥ 3, then the corresponding RT treatment will be considered safe and the evaluation of efficacy for this study arm will proceed.

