### Number of participants with rationale

Approximately 60 patients in total will be randomized, considering on average 1–2 lesions and a maximum of 3 lesions per patients (a mix of small and large lesions can be treated on a same patient), corresponding to the total of 96 lesions required (48 per study arm) (Fig. 1**,**
Fig. 2). Lesion sample size and power calculations have been performed in EAST v6.5, Cytel Inc, Massachusetts, USA.

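### An arm that passes the 13-lesion safety look has no stated decision point before lesion 48, although an 8th grade 3 or higher lesion already settles the result

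*Protocol article*

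**What the plan says.** The section on safety evaluation, which applies to each arm separately, states: "The safety will be evaluated based on a Simon’s two-stage design". The unacceptable rate is set by "considering as unacceptable, a rate of 25" per cent, the target is "evaluated at π^s^_1_ = 10" per cent, and the test is "at a one-sided 5 % type I error and power of 80" per cent. The number of lesions is given under the participant rationale: "corresponding to the total of 96 lesions required (48 per study arm").

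Two decision points follow. At the first, if "more than 10 lesions in the first 13 evaluated lesions do not present with skin toxicity" of grade 3 or higher, then "the study arm will continue to accrual completion". At the second, the condition for calling the treatment safe and moving on to efficacy is "If more than 40 out of the 48 lesions, do not present with skin toxicity" of that grade.

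The Planned timeline section adds that early closure is possible at the interim analysis if three or more such toxicities arise among the first 13 lesions assessed. No section of the article names a decision point between lesions 13 and 48.

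**The concern.** Restated as toxicity counts, the rule allows at most 2 events in 13 lesions and at most 7 in 48. The 8th event therefore fixes a negative safety result wherever it falls. Lesions treated in that arm afterwards cannot change the safety result. They also cannot open the efficacy test, which the article makes conditional on passing safety. They still add descriptive information on toxicity, local control and the secondary endpoints.

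What is at stake is the number of lesions treated in an arm that the plan can no longer call safe. The article presents the trial as the first randomized evaluation of FLASH radiotherapy with curative intent. After the interim it does more than stay silent, because its instruction is to continue.

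**Working it through.** **Inputs from the article.** n1 = 13, continue with 11 or more toxicity-free; n = 48, safe with 41 or more toxicity-free; toxicity rate q = 25% (null) and 10% (alternative); one-sided 5%; power 80%. Assumed here: lesions are independent and each outcome is known at once.

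**1. Reproduce the stated design.** The probability of passing stage 1 is the probability of at most 2 events in 13:

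(1−q)^13 + 13·q·(1−q)^12 + 78·q²·(1−q)^11

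- q = 0.25: 0.0238 + 0.1029 + 0.2059 = 0.3326, so the probability of stopping is 0.6674.
- q = 0.10: 0.2542 + 0.3672 + 0.2448 = 0.8661, so the probability of stopping is 0.1339.

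Summing over the stage 1 outcomes that pass, and requiring at least 41 of 48 toxicity-free in total, the probability of declaring safe is 0.0475 at 25% (type I error) and 0.8086 at 10% (power). A search over all two-stage designs with these error limits returns 10/13 and 40/48 as the Simon optimal design. The stated figures hold.

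Expected lesions as written are 13 + 35 × P(pass stage 1):

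- q = 0.25: 13 + 35 × 0.3326 = 24.6
- q = 0.10: 13 + 35 × 0.8661 = 43.3

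**2. When stage 2 is settled.** The 8th event can come as early as lesion 19 (2 in the first 13, then 6 in a row), leaving 48 − 19 = 29 lesions. The probability of passing stage 1 and then failing is P(pass stage 1) − P(safe):

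- q = 0.25: 0.3326 − 0.0475 = 0.285
- q = 0.10: 0.8661 − 0.8086 = 0.058 (0.0576 before rounding)

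A lesion-by-lesion recursion gives the mean number of lesions left at the 8th event, among arms failing in stage 2, as 11.9 at 25% (mean position 48 − 11.9 = 36.1) and 5.8 at 10%. At 25%, an arm that has passed stage 1 meets its 8th event before lesion 48 with probability 0.278/0.333 = 0.84.

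**3. Effect of acting at the 8th event only.**

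- q = 0.25: 24.64 − 0.285 × 11.9 = 24.64 − 3.39 = 21.2 lesions
- q = 0.10: 43.31 − 0.0576 × 5.76 = 43.31 − 0.33 = 43.0 lesions

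Expected toxic lesions at 25% are q times expected lesions: 0.25 × 24.64 = 6.2 as written and 0.25 × 21.25 = 5.3 with this change.

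**4. If the stage 1 count is read only at lesion 13.** At 25%, arms stopping at stage 1 have on average 4.39 lesions left when their 3rd event occurs, which adds 0.6674 × 4.39 = 2.93. Acting at both points gives 24.64 − 3.39 − 2.93 = 18.3 lesions. At 10% the result is 42.6.

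**5. Error rates.** Every path that stops early would have failed at 13 or 48 anyway, and no passing path is affected. Type I error stays at 4.75% and power at 80.9%.

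**6. Readout delay.** If accrual is uniform, 96 lesions over 30 months in two arms is 96/(30 × 2) = 1.6 per arm per month, or about 2 in the six-week toxicity window. With a 2-lesion overrun, acting on stage 2 alone gives 21.8 at 25% instead of 21.2, and acting on both gives about 20 instead of 18.3.

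**The case against.** Reading a Simon design at two fixed points is how that design normally works, and this one is correctly derived. A reader might infer that the safety calculation is wrong. It is not, and that part of the objection stands in full.

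A reader might also infer that the arm certainly goes on accruing after a 3rd event in stage 1. The article does not establish this. Its Planned timeline section expresses the closure condition as a count that the 3rd event can satisfy before all 13 lesions are assessed. The same sentence ties closure to the interim analysis and calls it only possible, so the text is unclear either way. This matters for the size of the point: at 25%, 2.9 of the 6.3 lesions saved by acting at both stages depend on that reading.

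A third tempting inference is that nobody would be watching between lesions 13 and 48. The article is condensed, and continuing safety monitoring is commonly set out in a full protocol, which is not shown. The point concerns only the statistical rule as stated.

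Finally, ending one arm early has a price. The objectives include describing and comparing the arms, and the secondary endpoints run to 12 months. A stop at the 8th event shortens concurrent randomisation and makes the toxicity estimate depend on the outcome. This lowers the priority of the point but does not remove it. A stage 1 stop under the plan has the same effect on randomisation, and the cost arises only in an arm that has already failed its safety criterion.

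**Conclusion.** The point holds as a low-cost improvement. The firm part is stage 2: the article tells an arm that has passed the first look to accrue to completion, although an 8th event rules out a safe verdict and closes the efficacy test. At the rate the article calls unacceptable, this happens in 28.5% of arms, and acting on it saves about 3.4 lesions per arm on average (24.6 to 21.2). At the target rate the saving is about 0.3 lesions, so an acceptable arm is almost untouched.

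The stage 1 part is an ambiguity between two sections. If the count is read only at the interim, the combined figure is 18.3 at 25%.

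The sizes assume independent lesions and immediate readout. With up to three lesions per patient they are approximate, and the six-week window makes the savings upper bounds. The points at which the result is settled, the 3rd event within 13 and the 8th overall, depend on neither assumption.

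**What to change.** In the safety evaluation section, state that an arm's statistical safety decision is reached as soon as the plan's own cut-offs settle it (the 8th grade 3 or higher lesion overall, or the 3rd within the first 13), and is then acted on under the plan's existing process. Reconcile this section with Planned timeline, so that both say whether the counts are read when observed or only at 13 and 48 lesions. If the sponsor prefers to keep two fixed looks, the article should say so and give the reason, for example to preserve the descriptive comparison.

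The cost is one or two sentences and a running count of data already collected. No new threshold is introduced and the sample size does not change. In an arm that has already failed, the toxicity estimate becomes less precise and outcome-dependent, and concurrent randomisation and the secondary-endpoint comparison are shortened. The report should present that arm's estimate accordingly.

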### Hierarchically tested: Efficacy evaluation (for each study arm separately)

Regarding efficacy in each of the two arms, if the safety question is satisfied then the hierarchically tested primary endpoint local tumor control rate (π^e^; number of lesions without relapse over the total number of randomized lesions) will be evaluated in the 48 lesions in the specific arm, assuming that the targeted local tumor control rate is ≥ 90 % [9].

An exact Binomial design for single proportion will be used, at a one-sided 5 % type I error, and a power of 80 %, for testing a local control rate ≤ 75 % versus a local control rate of at least 90 %, on the 48 lesions in the corresponding arm. That is, we test the null hypothesis H_0_: π^e^_0_ ≤ 75 % versus the alternative H_1_: π^e^_1_ > 75 %, evaluated at π^e^_1_ = 90 %.

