### Planned timeline

The estimated duration of recruitment is 30 months with a completion date in the end of 2026, follow up is 12 months after last treated patient. A possible premature closure is possible in case of unforeseen toxicity at interim analysis, in case of ≥ 3 grade ≥ 3 in the first 13 evaluated lesions.

Ethical considerations

LANCE trial received ethical approval from Cantonal Ethics Committee (CER-VD), SwissEthics, Swissmedic and Federal Office of Public Health (OFSP). The Investigator is responsible for the conduct of the trial and will ensure that the trial is performed in accordance to the protocol and with principles enunciated in the current version of the Declaration of Helsinki [23], the guidelines of Good Clinical Practice (GCP) issued by ICH [24], the European Regulation on medical devices 2017/745 [25] and the ISO Norm 14,155 [26] and ISO 14971, the Swiss Law and Swiss regulatory authority’s requirement [27], [28], [29]. The competent ethics committee and Swissmedic will receive an annual safety report and be informed about study stop/end in agreement with local requirements. The trial is registered on Kofam.ch and Clinicaltrial.gov (NCT05724875).

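### Local control fails only on a biopsy-proven relapse, so a tumour that never clears, or regrows without a biopsy, scores as a success

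*Protocol article*

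**What the plan says.** Two places in the protocol article define the efficacy endpoint.

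- The efficacy evaluation section gives the rate as "number of lesions without relapse over the total number of randomized lesions". Each arm has its own exact one-sample test, one-sided at 5 % with 80 % power, which sets an unacceptable rate of 75 % against a target of 90 %. The analysis set is fixed in size: the test is run "on the 48 lesions in the corresponding arm".
- The Endpoints section supplies the event and the window: "Local control rate is censured by any histologically proven local relapse into the initial treatment field up to one year post randomization".

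Neither place requires a complete response or documented control at one year for a lesion to count as controlled, and neither names persistent tumour as a failure. Tumour response appears only among the secondary endpoints, through blinded review of photographs. The Planned timeline section states that "follow up is 12 months after last treated patient".

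**The concern.** A binomial test with a fixed denominator needs every lesion scored as success or failure. On the published text, the only route to failure is "any histologically proven local relapse into the initial treatment field up to one year post randomization". Two kinds of treatment failure do not meet that description:

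- **Persistence.** A tumour that never clears has not relapsed.
- **Regrowth without biopsy.** A regrowth that is plain on examination but never sampled is not histologically proven.

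Both would enter the numerator as local control. The trial is of curative intent, so these are failures of the treatment under test. The error runs in one direction: omitting true failures can only raise the observed rate and the chance of passing. Each arm is judged against a fixed 75 % and not against the other arm, so nothing offsets it. A regimen whose true control is no better than the unacceptable rate could be declared effective more often than the stated 5 %.

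**Working it through.** **Inputs (efficacy evaluation section).** n = 48 lesions per arm; unacceptable control p0 = 0.75; target p1 = 0.90; one-sided 5 %; power 80 %. The article gives no rate of persistence, unbiopsied regrowth, loss or death, so all rates below are assumptions.

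**Step 1: reproduce the plan's figure.** Let X be the number of lesions scored as controlled, X ~ Bin(48, p). The cut-off is the smallest r with P(X ≥ r | 0.75) ≤ 0.05.

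| Cut-off | Type I error at 0.75 | Power at 0.90 |
|---|---|---|
| ≥ 41 of 48 | 0.0611 | 0.898 |
| ≥ 42 of 48 | 0.0272 | 0.800 |

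The rule is therefore 42 or more of 48, and the stated 80 % power reproduces.

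**Step 2: true failures scored as control.** At true control 0.75 the expected number of failures is 48 × 0.25 = 12 per arm. Two simple models of misclassification bracket the effect.

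- *Fixed count.* Exactly m true failures are scored as control. The arm passes when true controls reach 42 − m, so the type I error is P(Bin(48, 0.75) ≥ 42 − m).
- *Proportional.* Each true failure is scored as control with probability u = m/12. The apparent control rate is 0.75 + 0.25u, and the type I error is P(Bin(48, 0.75 + 0.25u) ≥ 42).

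| Failures scored as control, m | Apparent rate, proportional | Type I error, proportional | Type I error, fixed count |
|---|---|---|---|
| 0 | 0.750 | 0.027 | 0.027 |
| 1 (u = 1/12) | 0.771 | 0.055 | 0.061 |
| 2 (u = 2/12) | 0.792 | 0.102 | 0.119 |

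Under the proportional model the error reaches 0.05 when u is about 7 %, that is 0.07 × 12 ≈ 0.9 lesion per arm. At u = 10 % it is 0.062 and at u = 20 % it is 0.129.

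**Step 3: lesions of unknown status, for contrast.** Suppose k lesions have no one-year assessment and the formula is applied literally, so that all k score as control. The remaining 48 − k have true control 0.75, and the type I error is P(Bin(48 − k, 0.75) ≥ 42 − k).

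| k | Type I error |
|---|---|
| 3 | 0.045 |
| 4 | 0.052 |
| 5 | 0.061 |

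The effect per lesion is weaker because most of these lesions would truly be controlled. The gap between 0.027 and 0.05 absorbs three of them.

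**Step 4: the opposite coding.** If the same k lesions are scored as failures and the rest have true control 0.90, power is P(Bin(48 − k, 0.90) ≥ 42): 0.67 for k = 1, 0.51 for k = 2 and 0.33 for k = 3.

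**The case against.** A reader might infer more than the article supports, in three ways.

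- **Lost, deceased and unassessed lesions count as successes.** The article does not say so. It is true that the denominator is all randomized lesions, whereas the safety rate uses treated lesions, so a literal reading keeps such lesions in and finds no relapse in them. But a lesion never assessed at one year has not been shown to be free of relapse and could as well be scored as not controlled. Rules for death, loss and missing assessments commonly sit in the full protocol or the SAP, neither of which is shown. Their absence here is no finding.
- **Relapses are censored, so failures vanish.** The word *censured* invites that reading, but the efficacy section rules it out: a relapse takes a lesion out of the numerator and leaves it in the denominator. It is a wording slip.
- **The binomial should give way to Kaplan-Meier.** This is a design preference and can loosen error control. With no censoring, the plain Greenwood one-sided 95 % lower bound at 41/48 is 0.854 − 1.645 × √(0.854 × 0.146 / 48) ≈ 0.770. That exceeds 0.75, so 41 of 48 would pass, and the exact type I error of that rule is 0.061 against 0.027 now.

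Two further objections have some force. Persistence would be seen, because blinded photograph review covers tumour response; but that is a secondary endpoint and does not change how the primary test scores the lesion. And no rate of persistence or unbiopsied regrowth is given, so the size of the bias is conditional. The direction is not: it follows from the stated failure event.

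**Conclusion.** The point holds for persistent tumour and for clinically evident regrowth without biopsy. Taken literally, the stated failure event excludes both, and the test is biased towards passing. At 75 % true control and the 42-of-48 rule, about one such lesion per arm lifts the type I error from 0.027 to about 0.055–0.061, above the nominal 5 %; two lift it to about 0.10–0.12. These figures assume independent lesions and an assumed number of misclassified failures. For lesions lost, unassessed or in patients who died, the conclusion is only conditional on a literal application of the formula with no rule elsewhere. The planned test and its sample size are sound on their own terms and reproduce. This should be fixed, and the remedy is a clearer endpoint definition, not a new analysis.

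**What to change.** Keep the exact binomial test on 48 lesions per arm and change three things.

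1. Define failure as persistent tumour or in-field recurrence by 12 months, histologically proven or, when no biopsy is obtained, clinically evident. Use the same definition in the Endpoints and efficacy evaluation sections.
2. In the Endpoints section, replace *is censured by* with *the failure event is*.
3. Report a sensitivity analysis in which lesions unassessed at 12 months are scored as failures.

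The cost is mainly wording, since follow-up already runs to 12 months. The reported control rate may be somewhat lower, because more true failures will be counted. Scoring unassessed lesions as failures costs much power (0.51 with two such lesions), so it should remain a sensitivity analysis and not become the primary one.
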